# Sinew acupuncture for knee osteoarthritis: study protocol for a randomized sham-controlled trial

**DOI:** 10.1186/s12906-018-2195-8

**Published:** 2018-04-23

**Keywords:** Sinew acupuncture, Sham acupuncture, Knee osteoarthritis, Pain, Randomized controlled trial, Protocol

## Abstract

**Background:**

Sinew acupuncture is a new modality of acupuncture in which needles are inserted into acupoints, ashi points or spasm points of sinew and muscles along the meridian sinew pathway. A previous observational study revealed that sinew acupuncture has immediate analgesic effects on various soft tissue injuries, including knee injuries. However, no rigorous trials have been conducted. This study aims to examine whether sinew acupuncture can safely relieve pain and symptoms of knee osteoarthritis (KOA) and improve patients’ functional movement and quality of life.

**Methods/design:**

A randomized, sham-controlled, patient- and assessor-blinded trial will be conducted to compare the efficacy of sinew acupuncture and sham acupuncture. Subjects will be assessed by the physician and acupuncturists. A sample of eighty-six eligible subjects will be randomized into either the sinew acupuncture group or the sham acupuncture group. The intervention will be performed in the Hong Kong Tuberculosis Association Chinese Medicine Clinic cum Training Centre of the University of Hong Kong by acupuncturists with over 3 years of acupuncture experience. Subjects will receive 10 sessions of interventions for 4 weeks, followed by a 6-week follow-up. The visual analogue scale (VAS) score at week 4 will be the primary outcome. The Western Ontario and McMasters University Osteoarthritis Index (WOMAC), Timed Up & Go Test (TUG), 8-step Stair Climb Test (SCT) and the 36-Item Short Form Survey (SF-36) will be secondary outcomes.

**Discussion:**

Sinew acupuncture is a potential alternative non-pharmacological therapy for KOA. This rigorous trial will expand our knowledge of whether sinew acupuncture reduces pain intensity and improves symptoms, functional movements, and quality of life of KOA patients.

**Trial registration:**

The study was registered at ClinicalTrials.gov (Identifier: NCT03099317) in March 2017.

## Background

Osteoarthritis is one of the leading causes of disability in the elderly worldwide [1, 2]. The knee is the most commonly affected site [3]. Hip and knee osteoarthritis was ranked the 11th highest contributor to years lived with disability globally [4]. A US population-based survey found that 30.8% of men above the age of 65 and 34.8% of elderly women have radiographic evidence of knee osteoarthritis (KOA) [5, 6]. A survey study with the same protocol conducted in China found that the prevalence of KOA in elderly men (27.6%) was similar, but the prevalence in elderly women (46.6%) was higher than that in the US study [6]. Furthermore, the two studies revealed that the prevalence of pain in KOA was 6.9% to 7.1% in elderly men and 11.6% to 15.4% in elderly women [6]. In 1997, the cost of osteoarthritis in the USA, Canada, UK, France, and Australia accounted for up to 1–2.5% of the gross national product in each of these countries [7]. Approximately one-third of direct osteoarthritis expenditures were from medications, mainly for pain-related agents [8]. The burden of osteoarthritis will continue to increase worldwide in the ageing population.

Knee pain largely affects KOA patients’ quality of life and is the major reason patients seek medical help and advice [9]. Many modalities of non-pharmacological, pharmacological and surgical therapies have been implemented to reduce pain in KOA patients, including acupuncture, exercise, non-steroidal anti-inflammatory drugs (NSAIDs), COX − 2 selective agents, and joint replacement surgery [10]. NSAIDs and COX-2 inhibitors are commonly prescribed medications [10] but are associated with an increased risk of gastrointestinal bleeding and cardiovascular events [10].

Acupuncture has been widely used for KOA, although large-scale randomized controlled trials have shown contradictory results [11–14]. The discrepancies are caused by various factors such as the characteristics of controls [15, 16] and the dose of acupuncture treatment [16]. Systematic reviews have indicated that acupuncture is beneficial for patients with KOA [17, 18] and that the effects of acupuncture last for over 12 months [19].

Sinew acupuncture, a specific modality of acupuncture, was named by [name]. It was developed following the principles of *Huangdi Neijing*, a classic Chinese medical text, in conjunction with clinical experience [20–22]. *Huangdi Neijing* means “taking the [points of] tenderness as acupoints”. Needles are inserted superficially at sinew points (spasm points, painful points, or acupoints close to or distal to the pain) along the meridian sinew pathway to achieve therapeutic effects [22, 23]. TCM treatments, based on the theory of meridian sinews, have recently been used for pain management [24–27]. Sinew acupuncture potentially reduces the risk of internal organ injuries. Sinew acupuncture generally causes less pain than traditional acupuncture, as it does not require deep insertion of needles or the Deqi sensation by manual manipulation of the needle, such as lifting, thrusting, twisting, and twirling [28].

Our previous observational studies have indicated that sinew acupuncture has immediate analgesic effects on soft tissue injuries at various locations (knee, elbow, back, neck and shoulders) [29]. As no controls were used in the previous observational studies, it is unclear whether the immediate analgesic effects are due to true effects or spontaneous remission of the tissue injury.

The proposed study aims to examine whether sinew acupuncture can relieve pain and symptoms of KOA and improve functional movement as measured by the visual analogue scale (VAS), the Western Ontario and McMasters University Osteoarthritis Index (WOMAC), the Timed Up & Go Test (TUG) and the 8-Step Stair Climb Test (SCT). We will also evaluate whether sinew acupuncture can improve quality of life (QOL) as measured by the 36-Item Short Form Survey (SF-36). Furthermore, we will evaluate the safety of sinew acupuncture in treating KOA. We hypothesized that sinew acupuncture can safely relieve pain, enhance functional movement and improve QOL in KOA patients compared to sham acupuncture.

## Methods/design

### Study design

A randomized, sham-controlled, patient- and assessor-blinded trial will be conducted to compare the efficacy of sinew acupuncture and sham acupuncture. Subjects will receive 10 sessions of interventions, either sinew acupuncture or sham acupuncture, for 4 weeks followed by a 6-week follow-up period. The interventions will be performed by acupuncturists with more than 3 years of experience in acupuncture practice. Subjects will be blinded to the intervention and assessed by independent assessors using the primary outcome measure, VAS, and the secondary outcome measures, WOMAC, TUG and 8-step SCT. The details of the study design are shown in Fig. 1.

**Fig. 1 Fig1:**
[figure not shown]
Flow diagram of the study protocol. Assessment measures will be performed as follows: (1) Pain: VAS (visual analogue scale) and WOMAC (Western Ontario & McMasters University Osteoarthritis Index); (2) Functional movement: TUG (Timed up & Go Test) and 8-step SCT (Stair Climb Test); (3) Quality of life: Short Form-36 (SF-36); (4) Credibility test (end of weeks 2 & 4); (5) Test of blinding success (end of week 4); (6) Patient diary (weekly)

### Study subjects

Subjects will be recruited from the Hong Kong Tuberculosis Association Chinese Medicine Clinic cum Training Centre of the University of Hong Kong, local nursing homes and community centres using advertisements in local newspapers. The eligibility of subjects will be assessed by the physician and acupuncturists using the criteria described below.

### Inclusion criteria

Subjects are eligible to participate if they meet the following criteria: (i) are male or female Hong Kong permanent residents aged 50 years or above; (ii) meet the Clinical Classification Criteria for Osteoarthritis of the Knee as recommended by the American College of Rheumatology, have knee pain, have radiologic findings of osteoarthritis with Kellgren and Lawrence Grades 2–4, and have less than 30 min of morning stiffness or crepitus on active motion and osteophytes as determined by history and physical examination; (iii) have either unilateral knee pain or bilateral knee pain; (iv) have experienced pain for at least 6 months and knee pain > 40 mm on a visual analogue scale (VAS; 0 to 100 mm) within the past 7 days; and (v) are able to read and write Chinese and sign the informed consent form.

### Exclusion criteria

Subjects will be excluded if they meet any of the following criteria: (i) are unable to walk; (ii) have a serious infection of the knee; (iii) have suspected tears in any ligaments or menisci or acute inflammation of the synovial capsule; (iv) have a history of trauma, ligament damage, fracture, or surgery on the knee(s) within 6 months, causing pain or functional problems (history of knee replacement will be excluded); (v) have a history of local tumour/malignancy at the knee; (vi) have physical or laboratory findings indicating infection, presence of autoimmune disease or inflammatory arthritis; (vii) have knee pain caused by radiculopathy/herniation of an intervertebral disc; (viii) have end-stage diseases or other suspected severe conditions such as deep vein thrombosis of the lower limb, oedema related to cancer or cancer treatment, severe blood coagulation disorders, uncontrolled systemic arterial hypertension and severe diabetes; (ix) have a history of prolotherapy, hyaluronic acid injections or corticosteroids injections within 3 months; (x) have received acupuncture, electro-acupuncture, Tui-na therapy, massage, or physiotherapy 8 weeks prior to enrolment in the trial; (xi) have severe pain in other regions; (xii) have severe mental disorder(s); (xiii) are oversensitive to needles; and (xiv) are insensitive to pain due to advanced diabetes, neuropathy or use of strong painkillers.

Eligible subjects will receive baseline assessments and will be randomly allocated to the sinew acupuncture group (*n* = 43) or the sham acupuncture group (*n* = 43) in a ratio of 1:1 by block randomization. The random digits and letters will be generated by SPSS, covered by aluminium foil, and sealed into opaque envelopes.

Subjects will be advised not to receive other acupuncture treatments, Tui-na, massage or physiotherapy. Subjects are not restricted from the use of painkillers (including herbs) or external ointments if they suffer intolerable pain. The use of rescue medications, the daily level of morning stiffness and exercise time will be recorded in patient diaries.

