### Outcome measures

The VAS at week 4 will be the primary outcome. The WOMAC, TUG, 8-step SCT, and SF-36 scores will be the secondary outcomes. The assessment schedule is shown in Table 1. Independent assessors who are not involved in acupuncture treatments will perform the VAS assessments (asking subjects to indicate the pain intensity at the most painful points during walking and ascending/descending a step and overall). Acupuncturists will complete a “Physical Examination and Treatment Form” including details of the medical history, diagnosis and treatment procedures. The acupuncturists will communicate with the subjects using neutral language. The administration of analgesics, external ointments and herbal medicines and the time of daily exercises will be collected weekly from patient diaries during the intervention period and at each visit during the follow-up period.

**Table 1 Tab1:** The schedule of enrollment, interventions, and assessments

Items	Enrollment	Allocation (baseline)	Interventions (± 2 days)										Follow-up	
Time points (week)	-2	0	1			2			3		4		6	10
Treatment sessions (n)	–	–	1	2	3	4	5	6	7	8	9	10	–	–
Eligibility screen	✓													
Informed consent	✓													
VAS		✓	✓	✓	✓	✓	✓	✓	✓	✓	✓	✓	✓	✓
WOMAC		✓			✓			✓		✓		✓	✓	✓
SF-36		✓										✓		✓
TUG		✓						✓				✓	✓	✓
8-step SCT		✓						✓				✓	✓	✓
PE & Tx		✓	✓	✓	✓	✓	✓	✓	✓	✓	✓	✓	✓	✓
Patient Diary					✓			✓		✓		✓	✓	✓
Credibility Test								✓				✓		
Test of Blinding Success												✓		
Adverse events			✓	✓	✓	✓	✓	✓	✓	✓	✓	✓	✓	✓

PE & Tx, Physical Examination and Treatment Form; SCT, stair climb test; SF-36, 36-item short form; TUG, timed up & go test; VAS, visual analog scale; WOMAC, Western Ontario and McMasters University Osteoarthritis Index

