### Sample size estimation

G-power was used for sample size determination. The sample size was estimated by the VAS value with sinew acupuncture for knee pain using data from our pilot study [29]. The study observed 85 sessions of acupuncture treatments on the knee. After acupuncture treatments, the average VAS was reduced from 38.9 to 21.0 (change = − 17.9) with a standard deviation = 10.7. We estimated that the sham acupuncture (17.9*60% = 10.74) could reduce 60% of pain intensity compared to true acupuncture. The effect size was 0.673. With α = 0.05 and power (1-β) =0.8, the sample size was determined to be 37 per group. With the consideration of a 15% dropout rate, 86 subjects are required in each of the two groups.

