### Data analysis

All data will be doubly entered into a password-protected computer 1 week after data collection. The statistical analysis will be performed by SPSS 22.0 for Windows by a single statistician. The scores will be analysed by the intent-to-treat analysis. The last observation carried forward method will be used for missing data. Comparisons of continuous variables between the acupuncture and sham groups will be assessed using Student’s t-test or analysis of covariance (ANCOVA) with baseline measures as covariates. Comparisons of categorical data between groups will be tested by the χ^2^ test or the Mann–Whitney U-test. Changes in the scores from baseline within treatment groups will be assessed by the paired t-test or the Wilcoxon signed ranks test. Data from the patient diary will be assessed to analyse covariate balances in the two groups. If we find an imbalance, we will use the propensity score method [31] or the conditional inference method [32] to remove the confounding effect. All statistical tests will be two-sided at a 5% significance level.

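### Allocation at the week-0 baseline visit, before session 1 in week 1, lets subjects lost in between enter the week-4 analysis with zero change; opening the envelope at session 1 avoids this small dilution

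*Protocol article*

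**What the plan says.** The allocation paragraph, which closes the Exclusion criteria section of the Protocol article, states: "Eligible subjects will receive baseline assessments and will be randomly allocated to the sinew acupuncture group". Assignment is 1:1 by blocks, 43 per arm, from foil-covered assignments in sealed opaque envelopes. The article does not say when an envelope is opened or by whom.

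Table 1 (Outcome measures) has a week-0 column whose header begins "Allocation (baseline". Session 1 stands in a separate week-1 column, under an intervention block with a window of ± 2 days. No interval in days between week 0 and session 1 is given.

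The primary outcome is the VAS at week 4. The Measurement instruments section has the VAS taken before and immediately after every session, so a reading just before the first needling is already scheduled.

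The Data analysis section sets an intention-to-treat analysis and says: "The last observation carried forward method will be used for missing data". It makes no exception for a subject whose only VAS is the baseline one.

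**The concern.** Two rules that are harmless apart interact here. The schedule creates a period in which a subject is randomised but has not been treated. The missing-data rule then gives anyone who leaves in that period a week-4 VAS equal to the baseline VAS.

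Such a subject tells us nothing about either needling procedure. Yet each one adds a zero to an arm in which the plan expects a fall of 17.9 mm (sinew) or 10.74 mm (sham). The expected difference between arms shrinks and the spread within each arm grows, so power falls on both counts. Nothing in the article requires the arm to be known before the first needle is placed, so the exposure buys nothing.

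**Working it through.** **Inputs from the Protocol article**
- Mean VAS falls: sinew 17.9 mm; sham 10.74 mm, from "We estimated that the sham acupuncture (17.9*60% = 10.74) could reduce 60% of pain intensity compared to true acupuncture" (Sample size estimation). Difference: 17.9 − 10.74 = 7.16 mm.
- Spread of the change: "with a standard deviation = 10.7" (same section).
- Two-sided 5% level: "All statistical tests will be two-sided at a 5% significance level" (Data analysis).
- 43 per arm (allocation paragraph; the Abstract's total of 86 agrees). The Sample size estimation section puts 86 in each group. That is a separate inconsistency, not pursued here.

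**Assumption, not in the documents:** a fraction f of each arm, equal in both, is lost between allocation and session 1.

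**Step 1: the plan's own figure.** The article states: "With α = 0.05 and power (1-β) =0.8, the sample size was determined to be 37 per group". Its effect size ("The effect size was 0.673") is 7.2/10.7; unrounded, 7.16/10.7 = 0.669. A two-sample t-test (noncentral t) needs 37 per group at 0.669 (power 0.810; 36 gives 0.7995) and 36 at 0.673 (power 0.804). The 37 reproduces. The 15% dropout allowance gives 37 × 1.15 = 42.6, i.e. 43, or 37/0.85 = 43.5, i.e. 44. The planned 43 fits within one subject.

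**Step 2: add zeros.** If a fraction f of an arm with mean change m is set to zero:
- mean = (1 − f) × m, so difference = (1 − f) × 7.16
- variance = (1 − f) × 10.7² + f(1 − f) × m²
- standardised effect = difference / square root of the average of the two variances
- power from the noncentral t at 43 per arm

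**Step 3: worked case, f = 0.05** (about 2 per arm, since 0.05 × 43 = 2.15).
- Difference: 0.95 × 7.16 = 6.80 mm
- Sinew variance: 0.95 × 114.49 + 0.0475 × 17.9² = 108.77 + 15.22 = 123.98
- Sham variance: 108.77 + 0.0475 × 10.74² = 108.77 + 5.48 = 114.24
- SD: √[(123.98 + 114.24)/2] = 10.91
- Effect: 6.80/10.91 = 0.623; power 81.5%

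**Step 4: range**

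| Assumed loss before session 1, each arm | Difference (mm) | SD (mm) | Effect | Power at 43 per arm |
|---|---|---|---|---|
| none | 7.16 | 10.70 | 0.669 | 86.6% |
| 1 subject (1/43 = 2.3%) | 6.99 | 10.81 | 0.647 | 84.3% |
| 5% | 6.80 | 10.91 | 0.623 | 81.5% |
| 8% | 6.59 | 11.02 | 0.598 | 78.3% |

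**Step 5: what moving allocation recovers.** If randomisation continues until 43 per arm have attended session 1, power stays at 86.6%. If the lost subjects are not replaced, 42 per arm with no carried zeros give 85.8% (against 84.3%), and 41 per arm give 84.9% (against 81.5%). Every line assumes no dropout after session 1. The table therefore isolates this one mechanism and does not forecast the trial's power.

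**The case against.** Allocating after baseline and shortly before treatment is ordinary practice, and once a subject is randomised, intention to treat requires that the subject be counted. Both statements are right, and this is why the point is an improvement and not a correction. They do not argue against moving the allocation: a subject who leaves before session 1 would then never have been randomised, so nobody is excluded afterwards.

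The zero comes from the carry-forward rule, not from the allocation sentence. This is largely true. That rule acts on every dropout with no later reading, and moving the allocation leaves it in place for losses after session 1. But a different missing-data rule would still leave randomised subjects with no post-baseline data. Only the timing of allocation prevents that.

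The loss rates are not in the documents, and the gap may be a day or so. This stands in full. At one subject per arm and at 5%, power remains above the planned 80%. It falls below at 8%, which would place more than half of the 15% dropout allowance (8/15 = 53%) before the first needle.

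A reader might also infer that the acupuncturist's baseline examination is exposed to a known arm, because Table 1 ticks the Physical Examination and Treatment Form in the allocation column. The documents do not support this. The allocation paragraph names baseline assessments first and allocation second, the envelopes are sealed, and nothing says that the acupuncturist learns the arm at that visit. The form records history, diagnosis and treatment and is not an outcome. Independent assessors take the VAS, and the Discussion keeps the acupuncturist out of assessments and data entry. The article's silence on when the envelope is opened may simply be left to the full protocol.

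**Conclusion.** The point holds as a minor design improvement. By the article's own schedule, allocation precedes the first session, and by its own analysis rules anyone lost in between enters the week-4 comparison with zero change. At 43 per arm, power goes from 86.6% with no such loss to 84.3% with one subject per arm and 81.5% at 5%. These figures rest on the plan's assumed changes and SD, on equal loss in the two arms, and on loss rates that are illustrative only.

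Subjects are blinded and nothing suggests that one arm would lose more than the other before treatment. The expected consequence is therefore a diluted difference, not a bias between arms. It would be wrong to read this as an error in the randomisation, as a masking failure, or as a prediction that the trial falls short of its planned power.

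**What to change.** Keep all baseline assessments, including the acupuncturist's form, at week 0. In Table 1, move the allocation label from the week-0 column to session 1. In the allocation paragraph, add one sentence: the sealed envelope is opened at session 1, after the pre-session VAS has been recorded and immediately before needling. State that the week-0 VAS remains the baseline value, so that the extra reading before allocation causes no ambiguity.

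The visits, envelopes and scheduled measurements stay the same. Two small costs remain. The envelope must be at hand at the treatment session, a logistic detail that the article does not describe. And if 43 per arm are to be randomised, a subject who leaves before session 1 has to be replaced by another who has completed the baseline assessments.

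The handling of dropout after session 1 needs its own decision and is not settled by this change.

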### Interventions

#### Sinew acupuncture group

Subjects receiving sinew acupuncture will sit on a chair with the knee joint flexed at a most comfortable angle as close to 90 degrees as possible (if required, a block of A4 papers will be placed under the foot to adjust the angle). A hospital trolley table will be set up to block the vision of the subject to his/her knee (for blinding purposes). Routine disinfection will then be performed by the acupuncturist with a 75% alcohol pad. Acupoints (1–2 cm away from the point of tenderness, spasm or pain) along the meridian sinews near the knee(s) will be punctured through the skin by using sterile needles with a size of 0.30 mm × 40 mm (MOCM®) at an angle of 0–10 degrees pointing along the direction of the pain and the meridian sinew. The needles will be withdrawn immediately to a depth just under the skin and inserted forward smoothly 10 mm to 20 mm to avoid inducing pain. Five to eight points will be selected on each painful knee (while walking and climbing stairs) based on the theory of sinew acupuncture. Adjustments of the needles will be performed by extension and flexion of the knee joint to ensure that the needles do not cause pain during movement. Needles will be covered immediately by hypoallergenic bandages. The trolley table will be pulled away. Subjects will be advised to walk for 10 min (including the needle adjustment time). Needles will be adjusted at any time during walking if the subject has any pain induced by the acupuncture needle (for safety purposes) or primary pain of KOA (for the purpose of enhancing treatment effect). The trolley table will be used for blinding when the acupuncturist adjusts the needles. The acupuncturist will record the details of every adjustment procedure. After 10 min of walking, patients will be advised to step up and down from a step (~ 18 cm in height) for 12 rounds per knee. The pain points will be examined, and needle adjustments will be performed if necessary, followed by a period of rest by sitting for 5 min. After treatment, the needles will be removed while the subject is in a sitting position with the trolley table in place for blinding. Bandages will be applied in the same position for continuous blinding. The entire procedure will last 30 min per session. Subjects will receive 10 sessions of interventions for 4 weeks, starting with thrice a week during the first 2 weeks and then twice a week during the last 2 weeks. The above procedures will be performed by the acupuncturist and blinded to subjects.

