
#### Sham acupuncture group

Subjects in the sham acupuncture group will undergo the same procedures as those in the sinew acupuncture group except that the non-insertion sham acupuncture will be applied. Briefly, subjects will sit in a chair and their vision of their knees will be blocked by the trolley table. After disinfection, sterile needles with a size of 0.30 mm × 40 mm (MOCM ®) will be used to slightly puncture the acupoint without passing through the skin. The needles will immediately be covered with non-allergenic bandages to ensure sufficient blinding.

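### Stratifying by one versus two painful knees, and adjusting for it, would be a cheap gain in precision; its absence is not a bias or an error

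*Protocol article*

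**What the plan says.** All places are in the protocol article.

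- **Inclusion criteria:** patients qualify if they "have either unilateral knee pain or bilateral knee pain". The number of painful knees is therefore known before allocation.
- **Sinew acupuncture group:** "Five to eight points will be selected on each painful knee (while walking and climbing stairs". Needling is set per knee, not per patient.
- **Sham acupuncture group:** apart from non-insertion, sham patients "undergo the same procedures as those in the sinew acupuncture group", so their needle count also depends on the number of painful knees.
- **Exclusion criteria (allocation paragraph):** 43 patients per arm are allocated "in a ratio of 1:1 by block randomization". No stratification factor is named.
- **Data analysis:** continuous outcomes are compared by t-test or "analysis of covariance (ANCOVA) with baseline measures as covariates". The one stated balance check uses patient-diary data, which the allocation paragraph lists as rescue medication, morning stiffness and exercise time. Laterality is not among them.
- **Outcome measures and Measurement instruments:** VAS is rated at the most painful point in walking and in stepping, and overall. No index knee is defined, and all outcomes are per patient.

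**The concern.** Laterality does two things in this trial. It determines how many knees are treated, and it may predict walking pain, stair pain and function, because a second painful knee affects whole-person measures. A two-level factor of this kind, fixed at entry, is a natural candidate for stratification in a trial of 86 patients.

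Blocking without strata balances the arm totals but not laterality, so chance imbalance remains. If laterality is prognostic, that imbalance adds noise to the week-4 contrast which could be removed at almost no cost. What is at stake is some precision, and having the covariate fixed in advance rather than chosen once an imbalance has been seen.

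**Working it through.** **Inputs from the article:** 43 per arm (allocation paragraph); SD 10.7 mm, pilot reduction 17.9 mm and assumed sham reduction 10.74 mm (Sample size estimation); two-sided 5% level (Data analysis). The Sample size estimation section also speaks of 86 in each group. That conflicts with 43 per arm and is a separate matter; I use 43.

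**Inputs not in the article (assumed):** bilateral share p = 30-70%; bilateral patients D = 5-10 mm worse on the week-4 VAS.

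**1. The plan's own figure.** Difference = 17.9 - 10.74 = 7.16 mm; d = 7.16/10.7 = 0.669 (the article prints 0.673). A two-sided t-test with 80% power needs 37 per group at d = 0.669, as stated. At 43 per arm, power is 86.6%.

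**2. Needle counts.** One painful knee: 5-8 per session, 50-80 over 10 sessions. Two: 10-16 per session, 100-160 over 10 sessions. The ratio is 2 at equal points per knee, but individual pairs run from 10/8 = 1.25 to 16/5 = 3.2. The count per treated knee does not change.

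**3. Chance imbalance.** Taking the bilateral counts in the arms as two independent Binomial(43, p) variables:

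| p | P(gap of at least 6 patients) | P(gap of at least 8 patients) |
|---|---|---|
| 30% or 70% | 19.5% | 7.7% |
| 40% or 60% | 22.6% | 9.8% |
| 50% | 23.5% | 10.5% |

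A gap of 6 is 6/43 = 14 percentage points. The probability depends little on p.

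**4. Effect on the contrast.** Shift = gap × D: 0.14 × 5 = 0.7 mm and 0.14 × 10 = 1.4 mm, or 10-20% of 7.16 mm. The standard error of the arm difference is 10.7 × √(2/43) = 2.31 mm.

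**5. Power if the factor is accounted for.** Residual variance = 10.7² - p(1-p)D².

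- p = 0.3, D = 5: 114.49 - 5.25 = 109.24, SD 10.45, power 88.1%.
- p = 0.5, D = 5: 114.49 - 6.25 = 108.24, SD 10.40, power 88.4%.
- p = 0.3, D = 10: 114.49 - 21 = 93.49, SD 9.67, power 92.4%.
- p = 0.5, D = 10: 114.49 - 25 = 89.49, SD 9.46, power 93.4%.

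So 86.6% becomes about 88-93%. These are upper bounds, because baseline VAS would already carry part of the laterality difference.

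**6. Validity.** In 40,000 simulated null trials without stratification (p = 0.5), the t-test rejected in 5.2% (D = 5) and 5.0% (D = 10).

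**The case against.** The strongest case against is that nothing here is wrong. Unstratified block randomisation is valid. Laterality precedes randomisation and acts on needle count in both arms, so it causes no expected bias, and the standard error already allows for chance imbalance. A condensed article may also leave strata to the full protocol. The 5-10 mm gap is assumed, and its upper end exceeds the whole planned effect. The SD of 10.7 mm is reported with the pilot's change in VAS, and a stable laterality difference would largely cancel in change scores or under baseline adjustment, which the article already names as an option. All of this stands, and it limits the point to precision. It does not remove it: the article states its allocation method, covariates and balance check, and a better choice is available almost free.

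Three stronger readings are tempting, and the documents support none of them.

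- **That bilateral patients get a doubled dose in the sense that matters for response.** Only the total doubles, and only nominally. Each painful knee gets the same range of points, and two of the three VAS ratings are worst-point ratings.
- **That the Background shows dose to matter within this trial.** It lists "the characteristics of controls [15, 16] and the dose of acupuncture treatment [16" among the reasons why earlier trials disagree. That concerns differences between trials, and it does not say that dose means needle count.
- **That stratifying would show the effect at two dose levels.** A main-effect covariate does not do that. It would take a treatment-by-laterality interaction in a small trial, and needle count would still be inseparable from laterality.

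**Conclusion.** The point holds as a modest, cheap improvement in precision. The number of painful knees fixes how many knees are treated and is known at entry, yet the described randomisation, covariates and balance check do not use it. A gap of at least 6 of 43 patients between arms is expected in about one trial in five to one in four.

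The size rests on the assumed bilateral share and prognostic gap. Under them the contrast moves by less than its standard error, and the power gain is between about 1.5 and 7 percentage points at most. It is smaller after adjustment for baseline VAS and near zero if laterality is only weakly prognostic. The planned sample size is unaffected.

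**What to change.** 1. Stratify the block randomisation by one versus two painful knees as determined at baseline, using two sets of sealed envelopes.
2. Prespecify this factor, together with baseline VAS, as covariates in the primary ANCOVA of week-4 VAS. If allocation has already begun unstratified, the covariate alone can still recover most of the gain.
3. Report needles delivered per session by stratum, descriptively, from the Physical Examination and Treatment Form, which already records treatment details.

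Cost: a second envelope list, one degree of freedom and up to one incomplete block per stratum. No additional data collection should be needed, since the painful knees must be identified for treatment anyway. Neither the sample size nor the needling regimen changes.
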